### How will be blinding be achieved {24b}

Participant blinding will be achieved by ensuring that the experimental and sham training procedures are the same in appearance, duration, session structure, instructions, and mode of delivery. Both conditions will have identical computerized Go/No-Go tasks administered over six sessions across three consecutive days, using similar stimuli and response requirements, but different association contingencies. Participants will be informed that they will receive either an active or a sham version of the training, without disclosure of the specific feature of contingency distinguishing the two conditions.

Given that the intervention is designed to operate through implicit learning mechanisms by unconsciously forming associations between aggressive stimuli and inhibitory responses, it would not be appropriate to explicitly inform participants that the intervention targets aggression. Hence, the participant information sheet has described the study as follows: *“You are invited to participate voluntarily in a research study focused on providing a psychological intervention aimed at alleviating symptoms associated with substance use through the use of visual stimuli.” This will be cleared out at the end of the study when the participants will be informed regarding the true nature of the study and why it was required by the investigators to avoid disclosure of the same, at the beginning.* Prior to this and following the final follow-up, participants will be asked to guess their allocation group, either control or experimental, which will aid in assessing the effectiveness of the trial's blinding. They will also be asked about their perception of whether the intervention they received influenced their levels of aggression.

### Procedure for unblinding if needed {24c}

Unblinding of participants is not anticipated during the course of the trial, as the intervention is non-invasive and low risk. However, if carried out, any instance of unblinding will be documented, along with the reason and timing of disclosure. The primary investigator will have access to the group allocation of all enrolled participants.

## Data collection and management

### Plans for assessment and collection of outcomes {25a}

The outcome measures will be assessed at four time points: baseline (pre-intervention), 1-day post-intervention, 1-month post-intervention, and 3-months post-intervention. Pre-specified assessment windows have also been defined as follows: post-intervention (1 day), 1-month follow-up (± 4 days), and 3-month follow-up (± 7 days). All assessments will be administered by the primary investigator using standardized instruments, including the Overt Aggression Scale – Modified (OAS-M), Inhibitory Control Task, South Oaks Gambling Screen (SOGS), Alcohol, Smoking and Substance Involvement Screening Test (ASSIST v3.0), Timeline Follow-Back (TLFB), and the Stimulus Evaluation Task. These instruments have acceptable reliability and validity, with details of their psychometric properties described in the Methods section. To ensure consistency in questioning, questionnaires will be administered in Hindi following standardized translation procedures. All questionnaires will be asked in-person using an interview-style format with all participants to ensure that the data is complete and accurate. Data collection forms can be made available upon reasonable request to the corresponding author via email ([contact]).

The semi-structured proformas to be used in this study have been added to Additional file 3. The questionnaires for the Stimulus Evaluation Task, the Inhibitory Control Task, and the Inhibitory Control Training will be specifically developed for use in this study. Other questionnaires developed by other researchers to be employed in this study will also be appended to the same file—These questionnaires were either free to use or permission to use them in our study has been obtained from their authors.

Separate data collection forms will be created for baseline and for each follow-up time point. All data collection forms will be prepared using Microsoft® Word for Mac (Version 16.104) and stored in individual Word files for every participant. All assessments will be conducted in person by the primary investigator using an interview format. Questionnaires will be checked for completeness at the time of administration, allowing any missing or unclear responses to be clarified immediately.

### Plans to promote participant retention and complete follow-up {25b}

Participant retention will be promoted by conducting the intervention phase in an inpatient setting, allowing supervised completion of all training sessions. Follow-up assessments will be scheduled in advance, and participants and their designated family members will be contacted using previously obtained contact details to provide reminders during the week preceding each follow-up. Follow-up time points have been set up with windows to accommodate participants’ availability.

## Data management {26}

Data from our electronic word files will be copied and stored in Microsoft® Excel for Mac (Version 16.104) by the primary investigator. Periodic checks will be conducted for completeness and consistency. Range checks will also be implemented following data entry to ensure that the data values are appropriate. Final datasets will be secured and retained in accordance with institutional data management policies. All trial datasets will remain shared with the supervisor of the doctoral study (Corresponding Author).

## Confidentiality {33}

Personal and clinical information will be collected directly from participants during in-person assessments and recorded anonymously using unique study identification codes. Identifiable information, including consent forms and contact details, will be stored separately from study data in locked cabinets and password-protected digital devices accessible only to authorised members of the research team. Confidentiality will be maintained throughout the study and after its completion in accordance with institutional ethics guidelines.

## Statistical methods

### Statistical methods for primary and secondary outcomes {27a}

Initial analyses will summarize demographic and clinical data of the participants using descriptive statistics. Mean values and standard deviations will be used to describe baseline and outcome variables for the experimental as well as for the control condition across all assessment times. Prior to further analyses, t-tests (or equivalent non-parametric tests) will be applied to confirm equivalence between both groups in demographic characteristics and pre-intervention scores. Any initial differences will be considered for adjustment in subsequent analyses. Based on the normality of the data, parametric or equivalent non-parametric tests will be conducted to assess the differential effects of the intervention training compared to the sham training on each outcome variable over time. The primary outcome, overt aggression measured using the Overt Aggression Scale – Modified (OAS-M), will be analysed with time (baseline, 1-day post-intervention, 1-month post-intervention, and 3-month post-intervention) as the within-subjects factor and group (inhibitory control training vs sham training) as the between-subjects factor.

Secondary continuous outcomes will also be analysed using similar models. Outcomes expressed as categorical or binary variables (e.g., substance use or gambling presence) will be summarised as frequencies and proportions and analysed using appropriate analysis methods. All statistical analysis methds wil onl;y be decided upon once its ensures that our collected data meets the assumptions of the respective test. Harms will be reported descriptively.

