### Outcomes {16}

#### Study instruments for primary outcomes

The Overt Aggression Scale‐Modified [29, 30] is a semi-structured interview designed to evaluate various categories of aggressive behaviors. Four sub-components make up the overall aggression (AGG) score: Verbal Aggression, Aggression Against Object, Aggression Against Others, and Aggression Against Self. Subcomponent scores are determined by multiplying the number and severity level of aggressive behaviors of each type during the prior week. Additional scores include a Global Anger and Aggression (GAA) score composed of two item ratings: Subjective experience of anger and overt expression of anger. The OAS‐M has been shown to be reliable and valid, with good psychometric properties in terms of internal consistency, inter-rater reliability, test–retest reliability, face validity, convergent validity, divergent validity, and discriminant validity [30]. The primary outcome of the study will be the change in overall aggression score from baseline to the 1-Month post-intervention follow-up, as measured using the Overt Aggression Scale–Modified (OAS-M), and will be summarized using mean values and standard deviations.

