#### Sample size {19}

Drawing upon findings from Khan et al. [45], patients exhibited a significant reduction in aggression from a mean of 3.44 (SD = 3.89) to 1.07 (SD = 1.92) on the Overt Aggression Scale—Modified (OAS-M) after the computerized cognitive and social cognition training. The effect size was calculated using the G*Power software (Version 3.1.9.6) with a priori power analysis for a t-test comparing two dependent means (matched pairs) and an assumed correlation of 0.5 between paired measurements [46]. A paired t-test framework was used for effect size estimation because the control group (sham training) in this study serves primarily as a means of studying the mechanism of work of the ICT (i.e., 100% contingency-based associative learning), due to which we employed only 50% contingency between aggressive stimuli and no-go responses in the ST, which as suggested by some of the past literature, opposes how the ICT works [20, 23, 24]. However, recent studies have reported comparable effectiveness of sham and active inhibitory control training, raising uncertainty regarding the specificity of the proposed mechanism [47]. Similar concerns have also been raised in relation to attentional bias modification interventions, which were previously assumed to operate through similar mechanisms but have more recently been shown to give non-specific effects [48]. Therefore, to estimate the expected magnitude of change attributable to inhibitory control training itself, pre–post scores from the experimental condition were used for effect size calculation from prior literature.

According to the above estimates based on the prior literature, with a corresponding effect size of 0.70, power of 80%, and alpha of 0.05, the necessary sample size required to detect a comes out to be at least 26 subjects in each group (i.e., experimental and control) [49].

As per another study conducted at the same tertiary care centre as the current study [50], the dropout rate among patients was about 45% at 1 month, and another 15% increase in dropouts was reported at the 3-month follow-up. Thus, assuming a planned attrition rate of 60% in both groups using this reference, the overall required sample size for the research study is recalculated to 130 participants, with 65 participants in each group.

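### Baseline OAS-M is adjusted for only if a baseline test finds a difference, and a normality check picks the outcome test; a fixed baseline-adjusted model would be more precise and leave no choice open

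*Protocol article*

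**What the plan says.** All of the relevant rules stand in the protocol article, Statistical methods for primary and secondary outcomes {27a}.

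- Baseline: "t-tests (or equivalent non-parametric tests) will be applied to confirm equivalence between both groups in demographic characteristics and pre-intervention scores".
- Adjustment: "Any initial differences will be considered for adjustment in subsequent analyses". No covariate is fixed and no threshold is given.
- Choice of test: "Based on the normality of the data, parametric or equivalent non-parametric tests will be conducted to assess the differential effects of the intervention training". The section adds that methods will be settled only "once its ensures that our collected data meets the assumptions of the respective test".
- Primary model: OAS-M is analysed by group and time, "with time (baseline, 1-day post-intervention, 1-month post-intervention, and 3-month post-intervention) as the within-subjects factor". Baseline OAS-M is therefore one level of time and not a covariate.

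The primary outcome, under Study instruments for primary outcomes, is "the change in overall aggression score from baseline to the 1-Month post-intervention follow-up". Randomisation is unstratified {21b}, so baseline OAS-M is not balanced by design. Under Who will be blinded {24a}, one unblinded investigator enrols, treats, assesses and analyses.

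**The concern.** Three things are wrong with this sequence.

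1. With concealed random allocation, any baseline difference is due to chance. A test of that difference tests a hypothesis already known to be true, and a non-significant result at this sample size does not show that the groups are equivalent.
2. Whether a covariate belongs in the model depends on how well it predicts the outcome, not on whether it happens to differ between arms. Baseline OAS-M is the obvious prognostic variable for later OAS-M, and under this rule it would rarely be used as a covariate.
3. Both the covariates and the type of test are left open until the data are in, and the person who decides knows the allocation.

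What is at stake is power in a trial that expects about 45% dropout by 1 month, the primary time point, and the credibility of a result whose model was not fixed beforehand.

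**Working it through.** **Inputs.** From Sample size {19}: OAS-M mean 3.44 (SD 3.89) before and 1.07 (SD 1.92) after; correlation r = 0.5; effect size 0.70; alpha 0.05; 26 per group; 60% attrition; 65 per group. Assumed here: baseline tests at the 0.05 level, two-sided outcome tests, and 0.70 SD read as a between-group difference. The protocol's 0.70 is a within-arm pre-post effect, so the last assumption is for illustration only.

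**The plan's own figure.** SD of the paired difference = √(3.89² + 1.92² − 2 × 0.5 × 3.89 × 1.92) = √11.35 = 3.369. Effect size = (3.44 − 1.07)/3.369 = 0.703, so 0.70 reproduces. Then 26/(1 − 0.60) = 65 per group, 130 in total. (26 per group reproduces only as a one-sided two-sample test; a two-sided one needs 34. That is a separate matter.)

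**How often adjustment would be triggered.** Under randomisation a 0.05-level test is significant in 5% of trials. Simulation at 26 per group gave 4.6% to 5.4%. In about 95% of trials baseline OAS-M would not become a covariate. If ten independent baseline variables were tested at 0.05, the chance of at least one spurious difference would be 1 − 0.95¹⁰ = 0.40. The protocol states neither the number of variables nor the level, so this figure is an assumption.

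**Precision, equal SDs (in units of SD²).**
- Change score: 2(1 − r) = 2 × 0.5 = 1.00
- ANCOVA: 1 − r² = 1 − 0.25 = 0.75
- Ratio: (1 + r)/2 = 0.75

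**Power, difference 0.70 SD, two-sided 0.05, 26 completers per group.**

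| r | Change score | ANCOVA |
|---|---|---|
| 0.3 | 0.55 | 0.74 |
| 0.5 | 0.70 | 0.81 |
| 0.7 | 0.89 | 0.93 |

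A simulation of the rule itself (adjust only if baseline p < 0.05) at r = 0.5 gave power 0.70 to 0.71, against 0.81 for ANCOVA every time. The SD of the estimate was about 0.27 against 0.24. With 45% lost by 1 month, 65 × 0.55 = 35.75 remain per arm; at 35 per arm the calculated power is 0.82 against 0.92 (r = 0.5).

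**Precision, unequal SDs (r = 0.5).**
- Both arms with follow-up SD 1.92: change 11.35; ANCOVA 1.92² × 0.75 = 2.76; ratio 0.24.
- Sham follow-up SD stays at 3.89, ICT 1.92: mean change variance = (15.13 + 11.35)/2 = 13.24. Mean follow-up variance = (15.13 + 3.69)/2 = 9.41. Mean covariance = (7.57 + 3.73)/2 = 5.65. ANCOVA = 9.41 − 5.65²/15.13 = 7.30. Ratio 7.30/13.24 = 0.55.

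**Type I error.** The conditional rule, applied mechanically, gave 0.038 to 0.048 (r = 0.5 and 0.7). Choosing between t-test and Mann-Whitney by a Shapiro test on skewed data gave 0.046. By contrast, if any of four analyses (follow-up score, change score, ANCOVA, Mann-Whitney on change) could be picked after seeing the results, the chance that at least one reaches p < 0.05 under the null was about 0.106 (r = 0.5, 26 per group).

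**The case against.** The strongest reply is that the plan already uses baseline. It is a level of time in the primary model, and the primary outcome is a change from baseline. This stands: a reader might infer that baseline OAS-M is thrown away in most trials, and it is not. The loss is relative to ANCOVA only.

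Other stronger readings are also tempting, and the document does not support them:

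- **That pre-testing inflates type I error.** Applied as a fixed rule, it did not. The exposure comes from free choice after the data are seen.
- **That the normality check leads to rank tests which ignore both baseline and the group-by-time question.** No rank test is named, and the stated aim is to compare the two trainings over time. Mann-Whitney on change scores compares change between groups and uses each patient's baseline. Nor does it clearly cost power against the t-test: with skewed counts, the protocol's means and SDs, sham unchanged and 36 per arm, simulated power was 91% for Mann-Whitney on change and 87% for the t-test on change.
- **That adjustment cuts the variance to 24%.** This needs the sham arm to share the follow-up SD of 1.92, which was observed alongside the treated mean of 1.07.
- **That normality is certain to be rejected.** SDs above the means suggest skewed scores, but they are raw scores from a cited study, not change scores or residuals from this trial.

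It is also true that the adjustment sentence says only that differences will be considered; the 0.05 threshold is inferred. An unseen analysis plan cannot answer the point, because Protocol and statistical analysis plan {5} states that the analysis plan is integrated in the protocol.

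**Conclusion.** The point holds as one of precision and of pre-specification. The baseline tests cannot do what they are meant to do, and conditional adjustment gives up most of what ANCOVA would gain. At the protocol's r = 0.5 with equal SDs, ANCOVA has 75% of the change-score variance; for a 0.70 SD difference with 26 completers per group, that is power of about 0.81 against 0.70. The gain is larger where follow-up SDs fall below baseline SDs, as in the figures cited for the sample size: a ratio of 0.55 if only the ICT arm's SD falls, and 0.24 if both arms' do. The figures rest on an assumed correlation at 1 month, an assumed 0.05 level for the baseline tests, and a between-group effect that the protocol does not itself state. The plan as written is not invalid, but it should be changed.

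**What to change.** In section {27a}:

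1. Delete the baseline significance tests and describe baseline by arm.
2. Adjust the primary and all secondary continuous analyses for the baseline value of the outcome, in every case. For OAS-M, use either ANCOVA at 1 month, or a mixed model of the three follow-up visits with baseline as covariate and the 1-month group contrast as primary. The primary outcome need not be redefined: with baseline as a covariate, analysing the 1-month score or the change to 1 month gives the same treatment contrast.
3. Replace the normality check with one inference method named now, such as robust (sandwich) standard errors or a permutation test of the adjusted estimate. Name one rank-based analysis as a sensitivity analysis.

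Other pre-specified choices, such as a longitudinal model with baseline means constrained equal, would also serve. What matters is that one is fixed before the data are examined.

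The cost is wording and an amendment through the route in Protocol amendments {31}. No extra data are needed, and Trial status expects enrolment to run to December 2026, so there is time to fix the model before analysis.

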### Who will be included in each analysis {27b}

The primary analyses will follow the intention-to-treat (ITT) principle, including all randomized participants in the groups to which they were originally allocated, irrespective of intervention completion or follow-up attendance. In addition, per-protocol analyses will be conducted as a secondary analyses, including only participants who complete all six intervention sessions and all follow-up sessions.

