### Methods for additional analyses (e.g. subgroup analyses) {27d}

After the completion of data collection, the data will be reviewed for suitability of the following analyses: Post hoc comparisons may be conducted for detailed analysis through between group and within group measures in case prior statistical analysis indicates significant differences. The moderating effect of changes in inhibitory control and stimulus devaluation immediately post intervention on changes in overt aggression behaviours at 1-month and 3-months post-intervention may be analysed.

The moderating effect of changes in inhibitory control and aggressive behaviour immediately following the intervention and at 1-month post-intervention on changes in substance use frequency and gambling behaviour at 1-month and 3-months post-intervention may be analysed.

If a significant dropout rate occurs during the study, an analysis can be conducted to identify any patterns or trends in the characteristics of participants who dropped out. This analysis can help understand potential reasons for dropout in terms of demographic, clinical, or other factors associated with higher dropout rates.

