### Protocol and statistical analysis plan {5}

The full trial protocol, including the statistical analysis plan, is being submitted for publication and will be publicly accessible upon publication. The statistical analysis plan is integrated within the protocol document. The same data will also be available the Clinical Trials Registry of India (CTRI). Any substantive deviations from the pre-specified analysis plan will be clearly documented and justified in subsequent publications.

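### The primary outcome is aggression change at 1 month, but the stated analysis spans four time points and names no 1-month contrast

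*Protocol article*

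**What the plan says.** Under Study instruments for primary outcomes, the protocol article fixes a single time point: "The primary outcome of the study will be the change in overall aggression score from baseline to the 1-Month post-intervention follow-up".

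Section {27a} then describes how the primary outcome is handled. It "will be analysed with time (baseline, 1-day post-intervention, 1-month post-intervention, and 3-month post-intervention) as the within-subjects factor", with "group (inhibitory control training vs sham training) as the between-subjects factor". The stated purpose is "to assess the differential effects of the intervention training compared to the sham training on each outcome variable over time". No visit is singled out and no contrast is named.

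Individual comparisons come up in section {27d}, among the additional analyses: "Post hoc comparisons may be conducted for detailed analysis through between group and within group measures in case prior statistical analysis indicates significant differences".

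Section {5} adds: "The statistical analysis plan is integrated within the protocol document". On the article's own account, then, no separate analysis plan exists in which the 1-month test might be defined.

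**The concern.** The outcome definition asks whether the arms differ in change at 1 month. The analysis, read naturally, asks whether the arms differ in their course over baseline, 1 day, 1 month and 3 months. These are different null hypotheses. A difference at 1 day or at 3 months alone breaks the second and leaves the first intact.

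Two things are at stake. First, a significant result could be reported for the primary outcome with no effect at the time point that defines it. Second, if the overall test is not significant, nothing in the article commits the investigators to a 1-month comparison, so a real 1-month effect could go without a formal test.

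**Working it through.** **Inputs from the protocol article**
- Time has 4 levels and group has 2 ({27a}), so the group-by-time term has (4 − 1)(2 − 1) = 3 df.
- Sample size {19}: "with a corresponding effect size of 0.70, power of 80%, and alpha of 0.05", correlation 0.5 between paired scores, 26 per group before attrition, 65 after.
- Dropout {19}: about 45% at 1 month and a further 15% by 3 months.

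**Reproducing the plan's figures**
- Effect size: (3.44 − 1.07)/√(3.89² + 1.92² − 2 × 0.5 × 3.89 × 1.92) = 0.703, matching 0.70.
- Inflation: 26/(1 − 0.60) = 65 per group, 130 in total, as stated.
- Expected to remain: 65 × 0.55 = 35.75, about 36 per arm at 1 month, and 65 × 0.40 = 26 at 3 months.
- The 26 per group does not follow from the paired test described. That is a separate matter; here 26 and 36 serve only as analysis sizes.

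**Assumptions not all in the article:** equal SDs and compound symmetry (hence sphericity), normal data, complete data at the stated n, two-sided 5%, and a between-arm effect of 0.70 SD. The article gives r = 0.5 only for the paired sizing. At r = 0.5 the SD of a change score, √(2(1 − r)), equals 1, so effects in SD of score and SD of change coincide.

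**Formulas**
- 3-df test: noncentral F with 3 and 3(2n − 2) df, λ = (n/2) × Σ(d_t − d̄)²/(1 − r), where d_t is the between-arm difference at each of the four times.
- 1-month change-score t-test: d = 0.70/√(2(1 − r)) = 0.70.
- 1-month baseline-adjusted comparison: d = 0.70/√(1 − r²) = 0.808.

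**No effect at 1 month**

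For 0.70 SD at one other visit only, Σ(d_t − d̄)² = 0.49 − 4 × 0.175² = 0.3675.
- n = 26: λ = 13 × 0.3675/0.5 = 9.555, df 3 and 150, rejection rate 0.727.
- n = 36: λ = 18 × 0.3675/0.5 = 13.23, df 3 and 210, rejection rate 0.870.
- n = 26 with r = 0.3: λ = 6.825, rate 0.57. With r = 0.7: λ = 15.925, rate 0.93.
- A 1-month contrast rejects 5% of the time in all these cases.

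Simulation at r = 0.5 for the 1-day-only case agreed: 0.726 (n = 26) and 0.871 (n = 36) for the 3-df test, 0.049 and 0.051 for the change-score test.

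**A real 0.70 SD effect at 1 month, r = 0.5, equal n**

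| Effect at 1 day / 1 month / 3 months (SD) | n per arm | 3-df test | Change score at 1 month | Baseline-adjusted at 1 month |
|---|---|---|---|---|
| 0 / 0.70 / 0 | 26 | 0.73 | 0.70 | 0.82 |
| 0.70 / 0.70 / 0.70 | 26 | 0.73 | 0.70 | 0.82 |
| 0.20 / 0.70 / 0.35 | 26 | 0.56 | 0.70 | 0.82 |
| 0 / 0.70 / 0 | 36 | 0.87 | 0.83 | 0.92 |
| 0.20 / 0.70 / 0.35 | 36 | 0.72 | 0.83 | 0.92 |

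The third row uses Σ(d_t − d̄)² = 0.6525 − 4 × 0.3125² = 0.2619, so λ = 13 × 0.2619/0.5 = 6.81.

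**The group main effect instead**

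This averages over all four times, including baseline. For a 1-month-only effect the mean difference is 0.70/4 = 0.175 and the SD of a four-score mean is √((1 + 3 × 0.5)/4) = 0.791. That gives d = 0.221 and power 0.12 at n = 26, so this test does not target 1 month either.

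**The case against.** The best reply is that {27a} prescribes no wrong test. It lists two factors, never uses the words interaction, ANOVA or omnibus, and says methods will be settled after assumptions are checked. A mixed model with the same factors could yield the 1-month contrast directly. This stands: the 3-df test is the natural reading, not a stated rule, and the defect is an unnamed contrast. It does not remove the mismatch, since neither the interaction nor the group main effect isolates 1 month.

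Three stronger readings are tempting and are not supported.
- A reader might infer that the analysis will generally miss a real 1-month effect. The article defines the outcome as change, so a change-score test is the natural comparator. Against it the 3-df test loses nothing when the effect is at 1 month only or fully sustained. Setting 56% at 26 per arm against 92% at 36 would mix sample size, test and covariate adjustment.
- A reader might infer that only the 26 per arm with all four scores can be analysed. That holds for a classical complete-case repeated-measures ANOVA without imputation, which would drop about 36 − 26 = 10 per arm who have the 1-month score. But {27a} names no model, {27c} leaves the imputation method open, and {27b} promises an analysis "including all randomized participants in the groups to which they were originally allocated, irrespective of intervention completion or follow-up attendance".
- A reader might infer that {27d} makes the primary comparison conditional on an overall test. It speaks of post hoc comparisons in general. That the 1-month comparison is among them is an inference, made reasonable because no other route to it is given.

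Two further reservations. Additional file 2, Table S1, is cited for the primary outcome's metric and time point and was not available; it may bear on this. And OAS-M covers the prior week, so a difference confined to the 1-day visit may be less likely; the 3-month-only case gives the same 73%.

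**Conclusion.** The concern holds as a mismatch between the declared endpoint and its analysis. Nothing in the article ties the primary test to 1 month. On the natural reading, a 0.70 SD effect confined to 1 day or to 3 months produces a significant result 73% of the time at 26 per arm (57% to 93% for correlations of 0.3 to 0.7) and 87% at 36, where a 1-month contrast would reject 5% of the time.

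The loss of power for a real 1-month effect is conditional. At 26 per arm it is 56% against 70% (change score) or about 82% (baseline-adjusted) for a partly shared effect. For a 1-month-only or sustained effect, 73% is no worse than the change-score test, though still below baseline adjustment.

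The figures rest on equal SDs, sphericity, normal and complete data, and the effect patterns chosen. The mismatch does not depend on them. It should be settled before analysis, because it decides which result counts as success.

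**What to change.** In {27a}, name the between-arm difference in OAS-M aggression score at 1 month, two-sided 5%, as the single primary test. One suitable form is the 1-month contrast from a mixed model for repeated measures on all observed post-baseline scores, with baseline OAS-M as covariate and terms for arm, visit and arm-by-visit. Other baseline-adjusted 1-month comparisons would also serve.

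Make the 1-day and 3-month contrasts secondary, from the same model. In {27d}, state that the 1-month test does not depend on a significant overall test.

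The cost is wording, handled as an amendment to the analysis plan. It needs no extra participants, visits or measurements. The article expects enrolment to finish in December 2026 and plans all analyses after data collection, so the change can be made before any outcome analysis.
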